### SPA therapy treatment

Each spa therapy session will comprise a mineral hydrojet session at 37 °C for 15 min, the thigh manipulated under mineral water at 38 °C by a physiotherapist for 10 min, manual massages, the application of mineral matured mud at 45 °C to the knees for 15 min, and supervised general mobilization in a collective mineral water pool at 32 °C in groups of 8 patients for 15 min of 18 sessions, for 1 h each. Both groups will be mixed with the general public in the spa center. The spa therapist will not be aware of which patients will be taking part in the clinical trial. The experimental and active comparator arms will receive unrestricted non-pharmacological, pharmacological, and usual care during the study. Medication taken during or after the intervention will be reported in the follow-up questionnaires.

### Measures

At baseline, we will collect data on sociodemographic items (age, marital status, area living, education status), anthropometric measures, and co-morbidities association, according to OARSI guidelines.

### Primary outcomes

The primary outcome is change from effectiveness of the educational workshops, personalized and determined for every patient, measured by a GAS (Goal Attainment Scaling in Rehabilitation) [17] at 6 months, method of scoring the extent to which patient’s individual goals are achieved in the course of intervention. In effect, each patient has their own outcome measure but this is scored in a standardized way as to allow statistical analysis. Each goal is rated on a 5-point scale, with the degree of attainment captured for each goal area:If the patient achieves the expected level, this is scored at 0.If they achieve a better than expected outcome, this is scored at + 1 (more than expected), + 2 (much more than expected)If they achieve a worse than expected outcome, this is scored at − 1 (less than expected) or − 2 (much less than expected).

GAS depends on two things—the patient’s ability to achieve their goals and the clinician’s ability to predict outcome, which requires knowledge and experience. The process of the setting of the goals will be realized during the Initial educational assessment for each patient by specially trained nurses. For each patient, the main problem areas will be identify and establish an agreed set of priority goal areas (in connection with the themes of the workshops). Set goals should follow the SMART principle: they should be Specific, Measurable, Attainable, Realistic and Timely. GAS will be collected by clinical research fellow dedicated to this task that will be blinded.

### Secondary outcomes

Physical function is assessed by the Western and McMaster Universities Osteoarthritis Index (WOMAC subscale for physical function (W-TPFS)).Pain intensity during the last 24 h and the worst pain intensity during the last month are measured by a measured on a visual analog scale (VAS).Health-related quality of life (HRQOF) measured by the SF36, one of the most widely used generic measures of health-related quality of life.Comprehensive evaluation of patient education programs measured by a HEIQ. (Health Education Impact Questionnaire), an outcome and evaluation measure for patient education and self-management interventions for people with chronic conditions.

All the secondary outcomes will be collected at 6 months**.**

### Statistical considerations

#### Sample size estimation

According to the previous works presented in literature, we have estimated that a sample size of 105 patients per randomized group would provide 95% statistical power of highlighting an effect-size greater than 0.5 for a two-sided type I error at 5% for the primary outcome GAS T-score. Finally, a total of 250 patients (125 by group) will be considered to take into account lost to follow-up. With such sample size, a minimal absolute difference of 20% (50% versus 30%) can be shown for the secondary endpoint clinical improvement as defined in the thermarthrose [13] study for a power of 90%.

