#### Statistical analysis

Statistical analyses will be conducted using the Stata software (version 13, StataCorp, College Station, USA). A two-sided *p*-value of less than 5% will be considered to indicate statistical significance.

Concerning the primary outcome, the comparison between groups for univariate analysis will be analyzed using Student’s *t*-test or Mann-Whitney’s test. The normality will be studied by the Shapiro-Wilk test and the homoscedasticity using the Fisher-Snedecor test. Then, the analysis of the primary outcome will be completed by multivariable analysis using a linear mixed model to take into account: (1) fixed effects covariates determined according to univariate results and to clinical relevance (for example gender, age, analgesic treatments and season) and (2) center as random-effects (to measure between and within center variability). The normality of residuals will be studied as aforementioned. Intention-to-treat (ITT) analysis will be considered for the primary outcome, more precisely for all randomized patients except those without consent.

Other continuous endpoints (WOMAC, HEIQ, pain VAS, quality of life SF36, BMI) will be studied using the same statistical plan whereas the categorical parameters will be compared between groups with chi-squared or Fisher’s exact tests in univariate analyses and using generalized linear mixed model for multivariable analyses. For HEIQ and SF36 scores and pain VAS, the comparisons between groups will include in multivariable analyses the baseline values as independent parameters (fixed effects) as suggested by Vickers and Altman [18].

Longitudinal analyses concerning repeated measures at day 18 and months 3, 6, and 12 will be studied using random-effect models (linear or generalized linear), to take into account patient as random-effect (slope and intercept), nestled in center random-effect, while studying the fixed effects: group, time, and interaction *group x time*. According to clinical relevance, sub-group analyses depending the gender will be proposed after the analysis of interaction sub-group x randomization group in regression models (for repeated data or not).

Secondarily, a per-protocol analysis will be considered. A particular attention will be paid on number and duration of sessions and the type of intervention.

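### The 90% power quoted for clinical improvement (50% versus 30%) assumes almost no loss to follow-up; at the 105 per group needed for the primary outcome it is about 85%

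*Protocol article*

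**What the plan says.** Under Sample size estimation, the protocol article makes three statements in sequence.

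- For the primary outcome, "a sample size of 105 patients per randomized group would provide 95% statistical power" to detect an effect size above 0.5, "for a two-sided type I error at 5% for the primary outcome GAS T-score".
- The number is then raised: "a total of 250 patients (125 by group) will be considered to take into account lost to follow-up".
- It continues: "With such sample size, a minimal absolute difference of 20% (50% versus 30%) can be shown for the secondary endpoint clinical improvement", as defined in a cited spa-therapy trial, with 90% power.

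Under Statistical analysis, the general significance rule is "A two-sided *p*-value of less than 5% will be considered to indicate statistical significance". For categorical endpoints, "the categorical parameters will be compared between groups with chi-squared or Fisher" exact tests in the univariate step. Under Secondary outcomes, "All the secondary outcomes will be collected at 6 months". That list contains WOMAC physical function, pain on a visual analogue scale, SF36 and HEIQ. Clinical improvement is not on it.

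**The concern.** The step from 105 to 125 per group is there to absorb patients who will not provide outcome data. The next sentence bases a second power statement on the enlarged number and makes no allowance for loss. One paragraph therefore works with two evaluable numbers: 105 per group for the primary outcome and, in effect, 125 per group for clinical improvement.

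The secondary outcomes are collected at 6 months, the time point of the primary outcome, so the same losses can be expected to affect both. If they occur, the responder comparison has less power than stated. A non-significant result would then be taken as coming from a comparison with a 10% chance of missing a 20-point difference, when that chance was higher.

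**Working it through.** **Inputs**

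- Response rates 50% and 30%, stated power 90%, 125 randomised per group, 105 per group for the primary outcome: Sample size estimation.
- Two-sided 5% level: Sample size estimation (primary outcome) and Statistical analysis (general rule).
- 1:1 allocation: Abstract, and Randomization and allocation concealment.
- Chi-squared or Fisher's exact test: Statistical analysis.
- Loss rate: not stated. The implied allowance is 1 − 105/125 = 16%.

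**Step 1. What 105 represents.** For a standardised difference of 0.5, two-sided 5% and 95% power, the normal approximation is n = 2(1.960 + 1.645)²/0.5² ≈ 104 per group. The t-test solution is 104.9, which rounds up to 105. So 105 is the number needed with outcome data, and the further 20 per group are the loss allowance.

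**Step 2. Reproduce the 90%.** Two-proportion test with pooled variance under the null:

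power = Φ[(p₁ − p₂ − 1.960·SE₀)/SE₁], where SE₀ = √(2·p̄(1 − p̄)/n) and SE₁ = √((p₁(1 − p₁) + p₂(1 − p₂))/n), with p₁ = 0.5, p₂ = 0.3, p̄ = 0.4.

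At n = 125: SE₀ = √(0.48/125) = 0.0620 and SE₁ = √(0.46/125) = 0.0607. Then (0.20 − 1.960 × 0.0620)/0.0607 = 1.295, and Φ(1.295) = 90.2%.

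Solving for 90%: n = (1.960·√0.48 + 1.282·√0.46)²/0.20² = 124.0, that is, 124 per group. The stated figure is reproduced with 124 or 125 analysed per group.

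**Step 3. Apply the loss allowance.** At n = 105: SE₀ = √(0.48/105) = 0.0676 and SE₁ = √(0.46/105) = 0.0662. Then (0.20 − 1.960 × 0.0676)/0.0662 = 1.020, and Φ(1.020) = 84.6%.

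| Analysed per group | Power, pooled formula | Power, exact enumeration of chi-squared | Power, Fisher's exact |
|---|---|---|---|
| 125 | 90.2% | 90.0% | 87.6% |
| 124 | 90.0% | – | – |
| 120 | 89.0% | – | – |
| 115 | 87.7% | – | – |
| 110 | 86.2% | – | – |
| 105 | 84.6% | 84.9% | 81.5% |

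Other two-sided approximations at 105 per group also fall short of 90%: 85.6% with unpooled variance and 84.7% with the arcsine transformation. A one-sided 5% test would give 91.0% at 105, but the protocol specifies two-sided testing.

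**Step 4. Type II error, same test on both sides.** Exact chi-squared: from 100 − 90.0 = 10.0% at 125 to 100 − 84.9 = 15.1% at 105. Fisher's exact: from 12.4% to 18.5%. Either way the relative rise is about 50%.

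**Step 5. Detectable difference at 105 per group.** With p₂ = 0.30 and p₁ = 0.518, the Step 2 formula gives 90.1%; with p₁ = 0.517 it gives 89.8%. The difference detectable with 90% power is therefore 21.8 points, about 22.

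**Step 6. Could the analysis keep all 125?** Intention-to-treat is specified for the primary outcome. Imputation is left to a sensitivity analysis whose method will depend on the nature of the missing data. Neither provision makes 125 per group evaluable for clinical improvement at the assumed rates. Counting lost patients as not improved would lower both rates and change the calculation.

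**The case against.** The strongest defence is that no calculation in the section is wrong. The sentence refers to the sample size just given, 125 per group, and 125 per group yields 90%. The protocol does not claim that the 90% survives losses. This stands: the fault is an unstated assumption of complete data in a paragraph that has just allowed for incomplete data.

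Nor does the protocol say that it expects 105 evaluable patients per group, or 16% loss. It gives 105 as the requirement for the primary outcome, and 125 may include some rounding up. This also stands, so 85% belongs to full use of the allowance and is the lower end of a range.

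A reader might infer that the risk of a missed effect almost doubles, by setting Fisher's exact test at 105 per group (about 19%) against the stated 10%. That comparison mixes a change of test with the effect of losses, because Fisher's test already has 12.4% type II error at 125. The smallest expected cell count is 105 × 0.4 = 42, where chi-squared is the usual choice.

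A reader might also take the absence of clinical improvement from the outcome list as further evidence against the power figure. It is not. It is a separate inconsistency, and the endpoint is tied to a definition in a cited trial that cannot be checked here.

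Finally, this is a supplementary statement about a secondary endpoint and does not set the sample size. That is correct and limits its weight.

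**Conclusion.** The point holds as a minor correction. The stated 90% is right only if essentially all 125 patients per group are analysed; there is room to lose one per group. Power is about 85% if losses use the full allowance and between 85% and 90% if they are smaller. At the lower end, type II error is about 15% instead of 10%, and the difference detectable with 90% power is about 22 points instead of 20.

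This rests on three assumptions: the rates of 50% and 30%, a chi-squared test at two-sided 5%, and losses for clinical improvement similar to those allowed for the primary outcome. That 125 was the number behind the 90% is inferred from the order of the sentences and from the arithmetic.

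It would go too far to conclude that the trial is underpowered. The primary calculation, 105 per group raised to 125, is internally consistent and unaffected.

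**What to change.** Restate the sentence under Sample size estimation along these lines: *If 105 patients per group are evaluable, power for 50% versus 30% is about 85% (chi-squared, two-sided 5%), or 90% for a difference of about 22 points; 90% for 20 points assumes no loss.* It would help to state the assumed loss rate as well.

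Separately, reconcile the two sections on the endpoint. Either add clinical improvement, with its definition and time point, to Secondary outcomes, or remove the power statement.

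The cost is one sentence and one line in the outcome list. No additional patients are needed. The only price is a less favourable stated power for a secondary endpoint.

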#### Statistical analysis

Statistical analyses will be conducted using the Stata software (version 13, StataCorp, College Station, USA). A two-sided *p*-value of less than 5% will be considered to indicate statistical significance.

Concerning the primary outcome, the comparison between groups for univariate analysis will be analyzed using Student’s *t*-test or Mann-Whitney’s test. The normality will be studied by the Shapiro-Wilk test and the homoscedasticity using the Fisher-Snedecor test. Then, the analysis of the primary outcome will be completed by multivariable analysis using a linear mixed model to take into account: (1) fixed effects covariates determined according to univariate results and to clinical relevance (for example gender, age, analgesic treatments and season) and (2) center as random-effects (to measure between and within center variability). The normality of residuals will be studied as aforementioned. Intention-to-treat (ITT) analysis will be considered for the primary outcome, more precisely for all randomized patients except those without consent.

Other continuous endpoints (WOMAC, HEIQ, pain VAS, quality of life SF36, BMI) will be studied using the same statistical plan whereas the categorical parameters will be compared between groups with chi-squared or Fisher’s exact tests in univariate analyses and using generalized linear mixed model for multivariable analyses. For HEIQ and SF36 scores and pain VAS, the comparisons between groups will include in multivariable analyses the baseline values as independent parameters (fixed effects) as suggested by Vickers and Altman [18].

Longitudinal analyses concerning repeated measures at day 18 and months 3, 6, and 12 will be studied using random-effect models (linear or generalized linear), to take into account patient as random-effect (slope and intercept), nestled in center random-effect, while studying the fixed effects: group, time, and interaction *group x time*. According to clinical relevance, sub-group analyses depending the gender will be proposed after the analysis of interaction sub-group x randomization group in regression models (for repeated data or not).

Secondarily, a per-protocol analysis will be considered. A particular attention will be paid on number and duration of sessions and the type of intervention.

Finally, a sensitivity analysis will be performed and the nature of missing data will be studied (missing at random or not). According to this, the most appropriate approach to the imputation of missing data will be proposed (maximum bias (e.g., last observation carried forward vs. baseline observation carried forward) or estimation proposed by Verbeke and Molenberghs for repeated data).

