### Interventions

Both groups will receive a spa therapy during 18 days. Only the experimental group will receive the personalized self-management workshops. The aim is to propose a reinforcement of the spa therapy effect through 6 self-management workshops. The STT and the self-management workshops will be personalized and designed by expert spa therapy physicians. Interventions have been designed by a specialist steering committee, standardized and reproducible for all centers. The steering committee consists of investigators, a spa therapist, physician, and physiotherapist and the university hospital’s medical team (physician, physiotherapist, adapted physical activity instructor). Self-management program has been implemented since 2018 in Dax thermal care facilities. It aims to make the patients able to improve their quality of life by an accurate comprehension of their particular situation and participation in six workshops dedicated to get the necessary skills. The workshops aim at better understanding of the disease, use of drug treatments, nutrition, joint protection, and physical activity. The self-management program has been patronized by the French Association for Thermal Research (AFRETh) and was agreed by Nouvelle Aquitaine Regional Health Agency (ARS). A personalized educational diagnosis allows the identification of personal goals to be achieved by the patient.

Meetings with all members of the steering committee are organized to obtain consensus on the therapeutic protocol describing precisely the content and the organization of the intervention taking into account the context and the expertise of the different centers involved in the study.

A flow of the participants through the study is provided in Fig. 1.

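### The primary mixed model takes its covariates from trial results and an open list, which includes analgesic treatment without saying when it is measured

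*Protocol article*

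**What the plan says.** All places are in the Protocol article.

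- **Statistical analysis, first step:** "the comparison between groups for univariate analysis will be analyzed using Student’s *t*-test or Mann-Whitney’s test".
- **Statistical analysis, second step:** "the analysis of the primary outcome will be completed by multivariable analysis using a linear mixed model". Its fixed effects are "fixed effects covariates determined according to univariate results and to clinical relevance (for example gender, age, analgesic treatments and season"; centre enters as a random effect. The other continuous endpoints follow the same plan.
- **SPA therapy treatment:** both arms "will receive unrestricted non-pharmacological, pharmacological, and usual care during the study". On how drug use is captured, the same section says: "Medication taken during or after the intervention will be reported in the follow-up questionnaires".
- **Measures:** what is gathered before treatment is given in one sentence, which opens "At baseline, we will collect data on sociodemographic items" and goes on to body measurements and co-morbidities. Medication is not named.
- **Interventions:** "The workshops aim at better understanding of the disease, use of drug treatments, nutrition, joint protection, and physical activity". In Table 2 (Self-care workshops), one of the six workshops covers pain, fatigue and medical treatments.
- **Primary outcomes:** GAS is scored at 6 months, on goals tied to the workshop themes.

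The article does not say whether the analgesic covariate is a baseline or a follow-up value, or whether the unadjusted test or the mixed model decides the trial.

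**The concern.** There are two weaknesses in one sentence of the plan.

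First, the adjustment set depends on results from the trial itself, and the named variables are only examples. A separate analysis plan could supply a fixed list only by overriding this rule, so this is more than detail left for later. With an open list, several adjusted results are possible and nothing in the article singles one out.

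Second, analgesic treatment is among the examples. Use during follow-up may depend on allocation: care is unrestricted, and the workshops teach about drug treatment and pain. For some patients the scored goal might itself concern pain or medication. Conditioning on follow-up use would remove whatever part of the effect runs through it. It could also add bias from unmeasured causes shared by analgesic use and goal attainment. The adjusted coefficient would then answer a different question from the one the trial asks, which is the effect of adding the workshops to spa therapy.

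**Working it through.** **1. The plan's own figure (Sample size estimation).** Inputs: effect size 0.5, two-sided 5%, power 95%, 105 per arm, 125 per arm after losses.

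- n per arm = 2 × (1.960 + 1.645)² / 0.5² = 104 by normal approximation; the t-test gives 104.9, so 105.
- Power at 105 per arm = Φ(0.5 × √(105/2) − 1.960) = Φ(1.663) = 95.2%; t-test 95.0%.
- 105 / (1 − 0.16) = 125, an implied loss of 16%.

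The figure reproduces as a plain two-sample comparison. No covariate enters it.

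**2. When is analgesic use measured?**

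| Section | What it settles |
|---|---|
| Statistical analysis | Names the covariate, gives no time |
| SPA therapy treatment | Use during or after the intervention is recorded at follow-up |
| Measures | Baseline list does not name medication, but also omits gender and the baseline SF36, HEIQ and pain VAS that Statistical analysis uses or names |

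The baseline list is plainly incomplete, so its silence does not show that baseline use is uncollected. Follow-up recording is the only kind described, so entering a follow-up value remains possible under the text.

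**3. Data-driven selection and type I error.** Null simulation, 5000 runs, 105 per arm. Assumptions: 8 baseline covariates, each correlated 0.2 with the outcome; linear model without a centre effect; screening on association with the outcome at about p < 0.05. The article does not say which univariate results it means, so the screen is itself an assumption. Monte Carlo standard error near 5% is √(0.05 × 0.95 / 5000) = 0.3 points.

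| Analysis | Rejections at nominal 5% |
|---|---|
| Unadjusted | 4.6% |
| All 8 covariates, pre-specified | 4.8% |
| One mechanical screen | 5.0% |
| Smallest p among 11 models | 11.0% |

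The 11 models are the three above plus eight with one covariate each. A second simulation (n = 210 in total, 2500 nulls) gave 5.3% for a single screen, and 9.4% and 10.6% for the most favourable of all subsets of 4 and 6 covariates.

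**4. Adjusting for analgesic use at follow-up.** Let d be the reduction in the proportion using analgesics in the workshop arm, and b the loss in GAS (in SD) associated with use. Then

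adjusted effect = 0.5 − d × b, and power = Φ(adjusted effect × √(105/2) − 1.960).

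The documents give neither d nor b, so both are assumed. The residual SD is held at 1, and no unmeasured common causes are allowed for.

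| d | b | Adjusted effect | Power |
|---|---|---|---|
| 0.05 | 0.2 | 0.49 | 94% |
| 0.10 | 0.5 | 0.45 | 90% |
| 0.20 | 0.5 | 0.40 | 83% |
| 0.30 | 0.8 | 0.26 | 47% |

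If exactly one of d and b has the opposite sign, d × b is negative and the adjusted effect exceeds 0.5. The direction is therefore open as well as the size.

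**The case against.** **The analgesic covariate may simply be a baseline value.** It stands beside gender, age and season, which are not affected by allocation, and it is only an example. A reader might infer that the article records analgesics only after randomisation. It does not say so. It describes follow-up recording and is silent on baseline medication, in a condensed list that leaves out other variables the analysis needs. Data Availability says that a full protocol exists. This objection stands: over-adjustment is a risk that turns on an unstated time point, and it is not an established fault.

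**The first-line comparison is untouched.** The unadjusted test comes first, matches the sample size calculation and has neither weakness. This also stands. But the mixed model completes that comparison and is the only one of the two that accounts for centre, by which randomisation is stratified. Without a named decisive analysis, the adjusted result could carry the conclusion.

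**The rule as written hardly affects type I error.** Correct, at 5.0% to 5.3%. A reader might infer that the plan about doubles the error rate, but the 9.4% to 11.0% figures require reporting the most favourable of several models, which the plan does not propose. They show what an open list would permit.

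**Analysts are blinded** (Abstract, Methods and analysis). This limits steering towards a favoured arm. It does not hide whether a two-sided p-value falls below 5%, so the open choice remains.

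**Conclusion.** The point holds as a should-fix. The article states a rule that lets trial results determine the covariates of the primary mixed model. It leaves the list open, includes a variable that may be post-randomisation, and does not say which analysis decides. The harm lies in the freedom to choose among models and in the possible adjustment for a consequence of allocation; a single mechanical screen does little.

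No figure in the documents is wrong: 105 per arm and 95% power reproduce. The range of 0.49 to 0.26 SD for the adjusted effect (power 94% to 47%) rests wholly on assumed values and on follow-up use being the value entered. It illustrates the risk and does not estimate a bias. The documents do not support a stronger conclusion that the primary result is over-adjusted or invalid, because the timing is unstated and the unadjusted test is unaffected.

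**What to change.** Before unblinding:

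1. Delete the clause that lets univariate results determine the covariates.
2. Fix a short list of pre-randomisation covariates, for example age, sex and season of inclusion, plus centre. The particular list is the sponsor's choice; what matters is that it does not depend on the results.
3. Keep analgesic use only if a baseline value was already collected, and say that this is the value meant. Otherwise drop it. Randomisation began in March 2019 (Trial status), so a new baseline item could not be collected prospectively for patients already enrolled.
4. State that no variable measured after randomisation enters a model for the treatment effect, and report follow-up analgesic use as an outcome.
5. Name the decisive analysis of the primary outcome and make the other supportive.
6. Carry the same rule over to the other endpoints that use this plan.

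The cost is a few lines of wording, with no change to sample size or data collection.

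### Baseline adjustment is prespecified for HEIQ, SF36 and pain VAS but not for WOMAC physical function or BMI, and the longitudinal models name no baseline term

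*Protocol article*

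**What the plan says.** The Statistical analysis section sets out the primary analysis: a two-group test, then a linear mixed model with center as a random effect. The fixed covariates are picked from univariate results and clinical relevance, and gender, age, analgesic treatment and season are given as examples. It then extends this: "Other continuous endpoints (WOMAC, HEIQ, pain VAS, quality of life SF36, BMI) will be studied using the same statistical plan". The rule on baseline follows: "For HEIQ and SF36 scores and pain VAS, the comparisons between groups will include in multivariable analyses the baseline values as independent parameters". It cites a published recommendation for this form of adjustment.

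The longitudinal paragraph covers day 18 and months 3, 6 and 12. The fixed effects it names are group, time and group by time. Baseline appears neither as a response nor as a covariate.

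Under Secondary outcomes, "Physical function is assessed by the Western and McMaster Universities Osteoarthritis Index". No other listed outcome is presented as the measure of disability, which the Introduction names among the secondary objectives. Under Measures, the baseline data are sociodemographic items, "anthropometric measures, and co-morbidities association". No questionnaire is listed there.

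**The concern.** Five endpoints share one plan, and the baseline rule names three of them. Nothing in the text makes WOMAC function or BMI different in kind from the three that are named. The article is not merely silent here: it makes a rule and lists where it applies, so an analysis plan that followed it literally would treat WOMAC function differently from pain VAS.

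Two things are at stake. One is precision, if the baseline value stays out of the WOMAC model. The other is discretion: where the covariates depend partly on univariate results, the decision to adjust the disability outcome for its baseline may be taken after results have been seen.

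**Working it through.** **The plan's own figure.** The Sample size estimation section gives "a sample size of 105 patients per randomized group". Its inputs are a standardized difference of 0.5, power of 95% and a two-sided 5% test on the GAS T-score. The two-sample t-test gives n = 104.93, so 105 per group, with power 95.0% at 105. The figure reproduces. It concerns the primary outcome and is not in dispute. I use 105 per group below as the number evaluable.

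**Inputs.**
- From the documents: 105 per group, 1:1 allocation, two-sided 5%.
- Assumed, because the documents give neither: the baseline to 6-month correlation r, taken as 0.3, 0.5 and 0.7; and a true WOMAC effect of 0.4 SD.
- Also assumed: equal SD at baseline and follow-up.

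**Variance relative to an unadjusted final value (set to 1).**
- Baseline as covariate: 1 − r².
- Change score: 2(1 − r).
- Baseline as covariate relative to change score: (1 − r²) / [2(1 − r)] = (1 + r)/2.

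| r | Covariate, 1 − r² | Change score, 2(1 − r) | Ratio, (1 + r)/2 |
|---|---|---|---|
| 0.3 | 0.91 | 1.40 | 0.65 |
| 0.5 | 0.75 | 1.00 | 0.75 |
| 0.7 | 0.51 | 0.60 | 0.85 |

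Both comparators are shown because the article does not say whether these endpoints are analysed as final values or as change. Adjustment is the more precise at each r in either case.

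**Power for a 0.4 SD effect.** The effective standardized difference is 0.4 divided by the square root of the relative variance. For example, at r = 0.5 with adjustment it is 0.4/√0.75 = 0.462.

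| r | Final value, no baseline | Change score | Baseline as covariate |
|---|---|---|---|
| 0.3 | 82.2% | 68.4% | 85.6% |
| 0.5 | 82.2% | 82.2% | 91.5% |
| 0.7 | 82.2% | 96.1% | 98.1% |

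**Equivalent sample size.** Against a final-value comparison the factor is 1/(1 − r²): 1.10 at r = 0.3, 1.33 at r = 0.5 and 1.96 at r = 0.7.

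**Longitudinal models.** Take the mean of the four follow-up visits, with the same correlation r between all visits including baseline (a further assumption). The variance is (1 + 3r)/4 without baseline and (1 + 3r)/4 − r² with it.
- r = 0.3: 0.475 against 0.385, SE ratio 0.90.
- r = 0.5: 0.625 against 0.375, SE ratio 0.775.
- r = 0.7: 0.775 against 0.285, SE ratio 0.61.

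**The case against.** The strongest reply is that the plan does not leave WOMAC and BMI unadjusted. They get the same multivariable mixed model as the primary outcome, its covariate list is open, and baseline WOMAC is an obvious candidate on clinical relevance. This stands. A reader might infer that these two endpoints will simply be compared as raw 6-month values; the text does not support that. Baseline is neither required nor excluded, so the defect is that it is not prespecified.

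Second, the baseline sentence speaks of multivariable analyses without limiting them to month 6, so it can be read to cover the longitudinal models for HEIQ, SF36 and pain VAS. The effects named there may be those of interest rather than the whole model. This also stands. A reader might infer that no longitudinal model will be adjusted for baseline, but the text shows only that no such term is named.

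Third, if change scores are intended, the gain from adjustment at r = 0.7 is small: power goes from 96.1% to 98.1%. That is correct, and it is why both comparators are shown.

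Fourth, an article may leave full covariate lists to other documents. That would answer silence. It does not answer a stated rule that lists three of five endpoints.

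**Conclusion.** The point holds as a gap in prespecification on secondary endpoints. The baseline rule omits WOMAC function and BMI without a reason, and the longitudinal description names no baseline term.

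The cost is possible loss of efficiency and room for analyst choice. It is not bias: allocation is randomized and stratified by center, and the standard error already allows for chance imbalance. The primary outcome and its sample size are unaffected.

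For WOMAC function, a final-value analysis without baseline would need 1.10 to 1.96 times as many patients for the same precision as an adjusted one, if r lies between 0.3 and 0.7. This range and the 0.4 SD effect are assumptions, and the loss arises only if baseline is in fact left out.

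No power figure can be given for BMI. A reader might infer that a high baseline correlation leaves an unadjusted BMI comparison with little power. That does not follow: the power of an unadjusted final-value comparison depends on the effect and the SD, which the documents do not give for BMI, and not on that correlation. A high correlation only raises the benefit of adjusting.

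**What to change.** Replace the baseline sentence with one that covers every continuous secondary endpoint: for WOMAC, HEIQ, SF36, pain VAS and BMI, the baseline value is included as a fixed covariate, in both the 6-month and the longitudinal models.

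Confirm that WOMAC is recorded at baseline. The Measures section does not list it. It does not list HEIQ, SF36 or pain VAS either, yet the existing rule presupposes baseline values for those three, so joint collection is plausible but should be stated. BMI should be available from the baseline anthropometry.

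The cost is one sentence in the analysis section and, if WOMAC is already collected with the other questionnaires, no new visit or measurement. The change should be made before any comparison by group is seen.
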